### Phase 3: Iterative Prototyping and Testing

#### Overview

In this phase, the coconstruction committee will test the CHAMP prototype, providing feedback to guide the iterative refinement of its interface.

#### Approach

Coresearchers will participate in 3-5 sequential workshops, each lasting 2 hours. During these workshops, coresearchers will interact with the CHAMP prototype, engaging in live conversations to assess its performance and desired characteristics. Workshop activities will include (1) prototyping (evaluating CHAMP’s interface and structure at low fidelity) [60,61], (2) scenario testing (using hypothetical health scenarios to assess CHAMP’s functionality and decision logic) [62], and (3) the Wizard of Oz methodology (a simulated test where a human provides responses that users believe are automated to evaluate conversational flow, safety, and engagement) [63,64] (refer to Table 2). These activities will facilitate structured feedback on both preliminary usability (eg, navigation, responsiveness, and accessibility) and user experience (eg, tone, trustworthiness, and engagement) to identify optimal design solutions and interface options. Coresearchers will also complete validated measures of usability and acceptability after each workshop: the Usability Metric for User Experience-Lite [65] and the Acceptability E-Scale [66].

**Table 2. T2:** Prototyping, scenario testing, and Wizard of Oz.

Activity	Definition	Rationale	Application in CHAMP^a^	Outcome
Prototyping	Creating a simplified, early version of the system to test design ideas.	Low development cost and flexible iterative changes; helps identify and fix early design flaws before testing real-world tasks.	Coresearchers will interact with an early CHAMP prototype (eg, mock-up or partial build) to evaluate layout, flow, and content structure.	Rapid feedback on interface and interaction design at low fidelity.
Scenario testing	Using realistic, hypothetical scenarios to assess how users interact with a system.	Builds on the prototype with realistic user behavior; reveals whether the prototype can support users in actual information-seeking situations.	Coresearchers will be given hypothetical pediatric health scenarios (eg, fever and cough) and asked to use CHAMP to seek guidance.	Test functionality and decision logic in meaningful health scenarios.
Wizard of Oz	A simulated test where a human provides responses that users believe are automated.	Simulates fully functional interactions before system development is complete; allows nuanced testing of tone, safety, trustworthiness, and engagement with chatbot responses before investing in full development.	Coresearchers will exchange short text-based messages for 10‐15 turns, and an HCP^b^ team member simulates CHAMP responses in real time.	Validate user experience and refine human-computer interaction details. This process ensures CHAMP can deliver accurate, easy-to-understand, and professional responses.

a CHAMP: CHatbot to Assist the Management of Pediatric patients.

b HCP: health care providers.

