**Figure 1. F1:**
[figure not shown]
CHAMP (CHatbot to Assist the Management of Pediatric patients) multiagent architecture.

CHAMP will accept textual user input, all of which will be processed directly by the LLM without human involvement. User queries will be managed through a retrieval-augmented generation workflow that links inputs to the validated knowledge database and restricts responses to information within its scope. When inputs are ambiguous, poor-quality, or outside this domain, CHAMP will return a standardized clarification message (eg, “I don’t have information on that topic”). To ensure accessibility, CHAMP will be designed to interpret everyday language at an approximate grade 6 reading level, and no prior clinical or technical expertise will be required from users.

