### Patient and Public Involvement

Within a participatory paradigm, we will follow the Montreal model for patient engagement [47], embedding coconstruction as the central collaborative process in both research and chatbot development. Coconstruction positions partners as active coresearchers in shaping CHAMP by jointly defining priorities, informing key decisions about content and clinical logic, and grounding the tool in lived experience.

Youth, parents, caregivers, and partners will form a coconstruction committee (12‐15 members). Two groups will be engaged as coresearchers: (1) established partners from study conception and (2) newly recruited participants from Phase 1 (needs assessment). Following Phase 1, interested participants will be invited to join the coconstruction committee, bringing together existing and newly engaged partners. Coresearchers will participate in iterative workshops (Phases 2 and 3) to inform CHAMP’s development and broader research activities, including: (1) codeveloping grant applications; (2) attending team meetings; (3) informing study design, execution, and interpretation; and (4) coproducing knowledge dissemination products. Engagement intensity may vary over time for different members of the coconstruction committee [49]. To promote retention, we will emphasize shared ownership, regular communication, and flexible involvement, which are expected to strengthen members’ sense of commitment and ownership of the research [49]. Coresearchers will receive honoraria in accordance with the Strategy for Patient-Oriented Research Evidence Alliance and CHILD-BRIGHT Network guidelines [50,51]. A core aim is to build sustainable partnerships that extend beyond the study’s duration.

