## Results

This study is funded by the Unité de soutien au système de santé apprenant, Réseau universitaire intégré de santé et de services sociaux McGill, the Montreal Children’s Hospital MSSA Innovation Fund, and a Canadian Institutes of Health Research (CIHR) Operating Grant. The coconstruction committee is being assembled and includes 3 established partners and 5 newly recruited parent partners through the MUHC Partnership Office. As of December 2025, 4 initial meetings (held in February, March, April, and August 2025) have been completed. These meetings introduced CHAMP and gathered early insights on study design and data collection materials. They also generated input for the REB amendment and multilingual recruitment strategies. Participant recruitment for Phase 1 began in September 2025.

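### UMUX-Lite and AES are completed after every Phase 3 workshop, Wizard of Oz included, so scores meant to describe CHAMP can partly reflect replies written by a health care provider

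*Protocol article*

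**What the plan says.** The Approach section of Phase 3 (Iterative Prototyping and Testing) plans 3-5 "sequential workshops, each lasting 2 hours". It lists three workshop activities: low-fidelity prototyping, scenario testing with the prototype, and Wizard of Oz, described as "a simulated test where a human provides responses that users believe are automated". On the questionnaires it says: "Coresearchers will also complete validated measures of usability and acceptability after each workshop". These are UMUX-Lite and the Acceptability E-Scale (AES).

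The Wizard of Oz row of Table 2 explains that a health care provider "team member simulates CHAMP responses in real time". Its outcome cell states: "This process ensures CHAMP can deliver accurate", and goes on to two further qualities of the responses. For the working system, the CHAMP Technical Overview says of user input: "all of which will be processed directly by the LLM without human involvement".

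The Phase 3 Data Analysis section summarises both surveys with descriptive statistics and triangulates them with the qualitative data. Testing goes on until the research team judges usability and acceptability satisfactory. No numerical threshold is given.

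**The concern.** The two scales are meant to describe CHAMP, a tool that answers by LLM. The article fixes their timing by workshop, while what the coresearcher interacts with changes by activity: a mock-up or partial build, the prototype, or a person. A form completed after a workshop that includes Wizard of Oz partly rates that person's replies, and nothing in the stated analysis sets it apart.

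Two things are at stake. First, UMUX-Lite and AES are the only quantitative usability and acceptability measures named for Phase 3, and they measure the two constructs on which iterative testing ends. Ratings of human replies could therefore contribute to the judgement that the automated tool is satisfactory. Second, Table 1 lists functional improvement per iteration as an outcome. If the mix of activities differs between workshops, a change in score may reflect the activity and not the build.

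Table 2 carries a related error of inference. It presents a chat answered by a clinician as securing the accuracy of CHAMP's own responses.

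**Working it through.** The point concerns what a score measures. The article gives no expected scores, no number of Wizard of Oz sessions and no share of workshop time, so there is no figure to reproduce and no arithmetic to apply. The check is to set the statements side by side.

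1. **Timing of the scales.** Both follow each Phase 3 workshop, and no activity is excepted (Phase 3, Approach).
2. **Source of replies.** In Wizard of Oz it is a health care provider (Table 2). In the working system it is the LLM without a human (CHAMP Technical Overview).
3. **Analysis.** It is descriptive, giving the mean, median and SD as examples. No split by activity or by source of reply is stated (Phase 3, Data Analysis).
4. **Use.** Usability and acceptability decide when testing ends, in the judgement of the research team (Phase 3, Data Analysis).

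From 1 and 2, a form from a workshop containing Wizard of Oz partly reflects human replies. From 3, that form enters the summary on the same footing as the others. From 4, it can bear on the decision to stop.

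The article does not say how the activities are spread over the 3-5 workshops, so both arrangements need checking:

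| Arrangement | What a form rates | Can it be separated later? |
|---|---|---|
| Wizard of Oz fills a whole workshop | Human replies in that workshop, plus whatever interface is shown | Yes, if the analysis sets that workshop aside; the article does not say it will |
| Wizard of Oz shares a workshop with other activities | A blend of human replies, LLM replies and mock-up | No, because one form covers everything |

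Under both arrangements the stated rule lets human-written replies into the scores. Reporting workshop by workshop helps only in the first.

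The Table 2 claim can be checked without knowing the arrangement. If a provider writes the replies, their accuracy is the provider's. The activity can show which tone and conversational flow users respond well to. It cannot show that the LLM will produce accurate replies.

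**The case against.** The strongest case on the other side is that this is formative work with 12-15 coresearchers and no hypothesis test. The article calls the usability assessment preliminary. Study Limitations concedes that workshops only approximate real interactions, and a separate pilot usability test and an implementation-effectiveness study follow. The decision to stop rests on the team's judgement with triangulated qualitative data, not on a score. Table 2 presents Wizard of Oz as preceding completion of the system, so its scores may come before the builds on which the final judgement rests. Workshops are recorded and chats are time-stamped, so some separation may be possible afterwards. Form layout and version logging are also matters that an article may leave to the full protocol.

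Much of this stands, and it lowers the severity. It does not remove the point. The article does not merely omit a detail; it states a timing rule that covers every workshop. The order of the activities is not stated. Recordings cannot divide one form that covers a mixed workshop.

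A reader might infer that the deception must fail, because coresearchers are engaged in "informing study design, execution, and interpretation" and early committee meetings "gathered early insights on study design and data collection materials". The documents do not support that. General input on design does not show that a coresearcher knows when a person is replying. The committee was also still being assembled, with Phase 1 participants to join later. Nor is there a basis for requiring that the simulation be disclosed, since users' belief that replies are automated is part of how the article defines the method. Wizard of Oz is a legitimate formative technique, and its use is not the fault.

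**Conclusion.** The point holds, at moderate severity. As written, UMUX-Lite and AES scores from any workshop containing Wizard of Oz partly reflect human-written replies, are not separated in the stated analysis, and can contribute to the judgement that CHAMP is satisfactory. The word partly matters: navigation and other interface aspects still concern CHAMP whoever writes the replies.

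The size and direction of the distortion cannot be estimated. A reader might infer that clinician replies score higher and so flatter CHAMP. That is plausible for tone or trust, but the article gives no evidence for it, and a person typing live could score worse on responsiveness, which is one of the named usability aspects. A reader might also assume one Wizard of Oz workshop among the 3-5 and compute an affected share or a shift in a pooled mean. The article states neither the number of such workshops nor that scores are pooled across workshops.

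The conclusion rests on reading the timing rule as it stands, with no unstated exception for Wizard of Oz. The Table 2 accuracy claim is wrong as written and does not depend on that reading.

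**What to change.** In the Phase 3 Approach, give UMUX-Lite and AES directly after the scenario activity in which the live prototype answers by LLM. Alternatively, keep the present timing but give a form per activity and tag each with the activity, the source of replies and the build version.

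In the Phase 3 Data Analysis, state that the CHAMP usability and acceptability summary, and the judgement that a satisfactory level has been reached, use LLM-answered sessions only. Report any Wizard of Oz scores separately.

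In Table 2, reword the Wizard of Oz outcome to say that the activity informs the target tone and conversational flow, and remove the claim that it secures CHAMP's accuracy.

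The cost is a sentence or two, one table cell and a few fields on the form. The downside is somewhat fewer scores in the CHAMP summary. As of December 2025 the article reports only Phase 1 recruitment underway, so at that date the change could still be made before Phase 3 data collection.

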### Equity, Diversity, and Inclusion

To promote equitable participation, we will offer hybrid meeting formats (virtual and in-person) to support individuals living in remote areas or those for whom in-person attendance is challenging. Scheduling will consider diverse preferences, including individuals with nonstandard work schedules. Occasional asynchronous participation will also be supported through meeting recordings, emails, and phone interactions. We will offer live translation services and additional financial compensation for childcare responsibilities and transportation.

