#### Data Analysis

All workshops will be audio-recorded, transcribed verbatim, and deidentified. Transcripts, field notes, and observational data from the workshop activities will be analyzed using a hybrid inductive and deductive approach, with coding structured around established usability dimensions while generating themes [55]. The usability and acceptability surveys will be analyzed using descriptive statistics (eg, mean, median, and SD). Qualitative and quantitative data will be triangulated to identify design features that enhance or hinder usability and acceptability.

Given the nature of development, Phases 2 and 3 will be a continuous, iterative process. Rapid feedback cycles between workshops will inform continuous prototype refinements. The engineering team will modify the prototype between workshops to integrate user feedback. This process minimizes the risk of poor chatbot performance in interpreting user input and ensures that CHAMP delivers responses that are clear, accessible, and appropriate for a lay audience. Iterative testing will continue until CHAMP reaches a satisfactory level of usability and acceptability, as determined by the research team.

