### Sample Justification

The planned sample sizes reflect best practices for qualitative inquiry, participatory research, and pilot usability evaluation. The samples of Phase 1 (needs assessment) and Phase 4 (accessibility and multilingual adaptation), both of which involve focus groups with 20 participants, align with prior evidence that at least 3 focus groups with 5 participants capture 80% of themes and ensure acceptable data saturation [70]. For Phases 2 and 3, a cohort of 12‐15 coresearchers aligns with participatory design standards [71] and the minimum sample size recommended for pilot usability testing [72], promoting collaborative validation of chatbot content and function. Sustained engagement across phases ensures design continuity and depth of insight. In Phase 5, the ethnography prioritizes relational engagement, process dynamics, and lived experience, consistent with small-sample ethnographic traditions [68].

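### UMUX-Lite and Acceptability E-Scale scores taken after a workshop that includes Wizard of Oz partly or wholly rate a clinician's replies, not CHAMP's

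*Protocol article*

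**What the plan says.** **Timing and respondents.** The Phase 3 Approach section states: "Coresearchers will participate in 3-5 sequential workshops, each lasting 2 hours". It names the Usability Metric for User Experience-Lite and the Acceptability E-Scale and sets their timing: "Coresearchers will also complete validated measures of usability and acceptability after each workshop". Sample Justification gives the number of respondents: "a cohort of 12‐15 coresearchers aligns with participatory design standards".

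**What coresearchers try.** The same section says: "During these workshops, coresearchers will interact with the CHAMP prototype, engaging in live conversations". It then lists three activities: low-fidelity prototyping, scenario testing and Wizard of Oz. Table 2 describes the last as 10 to 15 turns of short text messages in which a health care provider on the team "team member simulates CHAMP responses in real time". The text and the table both define the method by the user's belief that the replies are automated.

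**Use of the scores.** Phase 3, Data Analysis, summarises the surveys descriptively and triangulates them with the qualitative data to find design features that help or hinder use. It has the engineers change the prototype between workshops, and adds: "Iterative testing will continue until CHAMP reaches a satisfactory level of usability and acceptability", with the research team as judge. Table 1 lists functional improvements per iteration among the Phase 3 outcomes.

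No section says which activity falls in which workshop, which system the scales refer to, or that scores are separated by activity.

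**The concern.** A usability score is informative only if one knows what was rated. The CHAMP Technical Overview defines CHAMP as a system in which a language model handles every input with no human in the loop. In Wizard of Oz the replies come from a clinician. The qualities on which Phase 3 seeks feedback, such as responsiveness, tone and trustworthiness, are ones that a clinician typing live would change.

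At stake is the per-iteration reading. If one workshop's score contains clinician replies and the next does not, a difference between them may reflect who wrote the replies and not the engineers' changes. The same scores measure the two properties, usability and acceptability, on which the team decides whether testing has gone far enough. Once a blended score has been collected, it cannot be split.

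**Working it through.** The plan states no figure for this point, so there is none to reproduce. The check tests the stated timing against each possible schedule, and then shows what can and cannot be sized.

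**Step 1. Does the missing schedule matter?**

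- *Wizard of Oz shares a workshop with the CHAMP prototype.* One end-of-workshop score covers both. If w is the weight of the Wizard of Oz exposure in the rater's judgement, score = (1 − w) × CHAMP rating + w × human-reply rating. Neither component is recorded, so the score cannot be decomposed.
- *Wizard of Oz has a workshop to itself.* Then w = 1, and that workshop's score concerns human-written replies only.

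Under either schedule the score is not a rating of CHAMP alone. What differs is whether it is blended or misattributed.

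**Step 2. Could the raters correct it?** Suppose the form told respondents to rate CHAMP. They believe the Wizard of Oz replies are CHAMP's, so they would include them. Only the order of administration, or a label applied by the team, can separate the two.

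**Step 3. How many scores are exposed?** Inputs: 12 to 15 coresearchers and 3 to 5 workshops.

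- Sets of scales in all: 12 × 3 = 36 to 15 × 5 = 75.
- If Wizard of Oz occurs in exactly one workshop (assumption): 1/5 = 20% to 1/3 = 33% of the sets.
- If it occurs in every workshop (assumption): 100%.

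**Step 4. How far could a workshop's mean move?** From Step 1, shift = w × d, where d is the gap between human-reply and CHAMP ratings in SD units. The article gives neither w nor d. As an illustration only, assume d of 0.3 to 0.8 SD in either direction:

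| Assumed w | Shift in that workshop's mean |
|---|---|
| 1/3 | 0.3/3 = 0.10 to 0.8/3 = 0.27 SD |
| 1 | 0.3 to 0.8 SD |

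The standard error of one workshop's mean, in the same units, is 1/√15 = 0.26 to 1/√12 = 0.29 SD. Under these assumptions a one-third blend stays within about one standard error (0.27/0.26 ≈ 1.0). A workshop of Wizard of Oz alone could shift by about 1 (0.3/0.29) to 3 (0.8/0.26) standard errors. The sign is open: a clinician's content may be rated higher, and the typing delay lower. These figures show the mechanism and do not estimate the bias.

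**The case against.** The best defence is that the article condenses a fuller protocol. Workshop agendas and form instructions belong there, and since the coresearchers converse with the prototype in these workshops, the prototype is the natural thing to rate. This stands as far as the schedule goes: the article does not show which workshops are affected. It does not remove the problem, because the timing is stated and, by Step 2, a form instruction cannot help a rater who believes the human replies are automated.

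It is also fair that the measures are descriptive, that Phase 3 calls the usability feedback preliminary, that the limitations section concedes workshops only approximate real use, and that a pilot usability test follows. The team knows which activity was Wizard of Oz when it reads the transcripts. All of this limits the consequence, but none of it makes the affected scores interpretable.

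Several stronger readings are tempting, and the article does not support them:

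- *Ratings of mock-ups are errors.* Table 2 treats a mock-up or partial build as an early form of CHAMP, and rating successive versions is normal formative work. A label is enough.
- *Members who only saw a recording rate a build they never used.* Equity, Diversity, and Inclusion says "Occasional asynchronous participation will also be supported through meeting recordings, emails, and phone interactions", but not that such members complete the scales.
- *A pooled CHAMP mean is biased by a known number of points.* Data Analysis does not say that scores are pooled across workshops.
- *The surveys are the stopping rule.* The text leaves that judgement to the research team and names no criterion.
- *These scales are the only quantitative outcomes of Phase 3.* Table 1 gives them as examples.

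**Conclusion.** The concern holds for Wizard of Oz. Following the stated timing yields scores that are blended or misattributed for every workshop in which that activity takes place, whatever the schedule. This weakens them as evidence on CHAMP per iteration and as possible input to the decision that testing may end.

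The conclusion rests on two things in the text: the fixed timing, and the definition of Wizard of Oz as human replies that users take to be automated. It also assumes that the scales are given after workshops containing that activity, as the word each implies. The number of affected workshops, the size of the bias and its direction cannot be derived from the article. No hypothesis test depends on these scores. The change is a cheap improvement worth making before Phase 3 begins, not a flaw that undermines the study.

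**What to change.** In the Phase 3 Approach section, replace the end-of-workshop timing with this rule: each coresearcher completes the two scales after hands-on use of the CHAMP prototype and before any Wizard of Oz activity in that workshop. If the scales are also given after Wizard of Oz, report those scores separately and not as CHAMP's. A workshop devoted to Wizard of Oz alone then contributes no CHAMP score.

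Have the team, not the respondent, record with each score the version rated: mock-up, identified build or Wizard of Oz. Tag Wizard of Oz turns in the stored chat histories. Data Privacy and Security describes the stored replies as CHAMP's output and allows deidentified histories to be used to refine the model, so untagged clinician text could pass for the chatbot's own.

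The cost is about one protocol sentence, one extra form field and slightly fewer ratings counted as CHAMP's. Memory of a Wizard of Oz session in an earlier workshop may still colour later ratings. The version record would at least let the team see where that could apply.
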